## 1 BACKGROUND INFORMATION

This is the third trial for the clinical development of intravenous (IV) GMI-1070. The trial will be conducted in compliance with the protocol, Good Clinical Practice (GCP), and applicable local and federal regulatory requirements. The subject population will comprise adults with stable sickle cell disease (SCD).

GMI-1070 is a pan-selectin antagonist, a compound found to inhibit selectin binding *in vitro* and to inhibit selectin-mediated effects *in vivo*. Selectin binding is a key early step in the inflammatory process leading to leukocyte adhesion and recruitment to inflamed tissue. Selectin binding has been shown to be involved in many disease processes that involve inflammation. There are no other known approved therapeutic agents in this class. This investigational product is being developed for the treatment of vaso-occlusive crisis (VOC) in SCD.

### 1.1 Sickle Cell Disease

SCD is one of the most prevalent genetic disorders in the United States (US), affecting over 80,000 people. It is a chronic condition with substantial morbidity and mortality, and is responsible for more than 75,000 hospitalizations per year in the US with an average stay of 6.1 days. Both children and adults are affected, and greater mortality is seen in those with more severe disease. The gene is found most commonly in people of African or Arab-Indian descent, and the disease is seen most commonly in these regions or in areas to which these populations have migrated, including the US and Europe.

SCD refers to a group of autosomal recessive inherited disorders of the  $\beta$ -globin gene. A single nucleotide substitution results in the presence of valine instead of glutamic acid in the  $\beta$ -globin chain. The resulting polymerization of hemoglobin S (Hb S) when deoxygenated is the primary indispensable event in the molecular pathogenesis of SCD. Individuals homozygous for Hb S have sickle cell anemia (SCD-SS). Those who are compound (double) heterozygotes have 1 copy of Hb S and 1 copy of either Hb C (SCD-SC), Hb  $\beta^+$ -thalassemia (SCD-S $\beta^+$ -thal), or Hb  $\beta^0$ -thalassemia (SCD-S $\beta^0$ -thal).

### 1.2 Vascular Occlusion in the Pathogenesis of Sickle Cell Complications

SCD is associated with a number of serious and potentially disabling conditions that have similar symptoms but vary in severity by genotype. The most notable complication of SCD is VOC, an extremely painful and serious consequence of SCD presumably resulting from acute ischemic tissue injury. Individuals with the SCD-SS and SCD-S $\beta^0$ -thal genotypes tend to experience similar disease severity, which is more severe than for other genotypes. SCD-SC and SCD-S $\beta^+$ -thal are associated with a milder form of the disease.

Over the course of a year, about 60% of patients with SCD-SS will have at least 1 severe VOC, which typically presents as episodes of pain and inflammation at 1 or more sites, of varying degrees of severity, and occurring at varying intervals throughout life. These pain crises, as VOC episodes are also known, are the clinical hallmark of SCD, and are responsible for the vast majority of hospitalizations (> 90%), and result in significant morbidity, mortality, and interruption of daily functioning. The onset of pain is unpredictable, and has been described as periodic, self-limited episodes of excruciating musculoskeletal pain (although visceral, soft tissue, and other locations have been reported), occurring as early as 6 months of age. Other problems include ischemic and hemorrhagic stroke, acute chest syndrome, splenic sequestration, dactylitis, osteonecrosis, priapism, leg ulcers, and nephropathy. Most SCD-related deaths occur during acute VOC, and are due to acute chest syndrome or stroke. Patients can become symptomatic with pain, infection, or splenic sequestration as early as 6 months of age; thus, VOCs are an important cause of morbidity and mortality throughout life, resulting in disruption of the individual's education, psychosocial development, and employment as well as causing severe pain, hospitalization, and premature death.

The etiology of VOC involves dual mechanisms: a mechanical component, by which the sickled red blood cells (RBCs) become caught in the post-capillary venules, and an associated inflammatory response in which white blood cells (WBC) adhere to the endothelium (Figure 1).

[figure not shown]

**Figure 1: Sickled Red Blood Cells and Neutrophils Occlude Vasculature**

The underlying pathogenesis of RBC sickling is the deoxygenation of Hb S, which results in polymerization of the hemoglobin, distortion of the RBC, and loss of deformability of the cell. These “sickled” RBCs are a primary component of the occlusive process and cause vascular injury through interactions with endothelial cells.

The other primary component is adhesion, since the stickiness of the cells causes cell aggregates of WBC-RBC, WBC-WBC, and WBC-platelet to form. This adhesion is selectin-mediated and contributes to the VOC process. Cell aggregates block the vasculature and create a trap for the sickled RBCs, resulting in obstruction of blood flow.

Finally, vaso-occlusion resulting from sickled and adherent RBCs also causes slowing of blood flow in post-capillary venules, local tissue hypoxia, and further tissue inflammation, resulting in more deoxygenation and sickling of RBCs, and propagation of the occlusion. This is sometimes called secondary recruitment of sickled cells and occluded vessels. Diapedesis (leukocyte migration into the tissues) and sickle-related microvascular occlusion also takes place in postcapillary venules. Pain is the result of initial and ongoing occlusion and ischemia and is thought to be nociceptive. It is particularly severe for patients with the SCD-SS genotype, who have been observed to have a higher mortality than other genotypes.

 Nociceptive pain is initiated by nociceptors, the nerves which sense and respond to damage (fractures, burns, bumps, bruises, and inflammation) in a particular part of the body. This differs from neuropathic pain, which is the result of an injury or malfunction in the peripheral or central nervous system (CNS).

Of note is that soluble E-selectin, vascular cell adhesion molecules-1 (VCAM-1), and intracellular adhesion molecules-1 (ICAM-1) levels are higher in sickle cell patients at baseline than in normal volunteers. Further evidence suggests that soluble E-selectin and ICAM-1 are increased during acute VOC when compared to baseline in patients with SCD. In addition, increased soluble E-selectin levels have been shown to correlate with increased mortality in SCD patients. Leukocytes adherent to the endothelial cell wall in postcapillary and collecting venules interact with sickled RBCs, leading to vaso-occlusion in sickle cell mice. However, sickle cell mice lacking E- and P-selectin were protected from developing vaso-occlusion. An understanding of the role that selectins play in cell aggregation and the pathophysiology of VOC is increasing.

### **1.3 Intravital Microscopy**

Intravital microscopy (IVM) is a non-invasive imaging technique used for studying dynamic cell interactions and microvascular morphometry in living tissue. Variations of this technique have been used to measure microvascular blood flow and perfusion in both human and animal studies for multiple diseases, including diabetes, cardiovascular disease, and more recently SCD. The methods used in humans are non-invasive and involve application of a probe to an accessible vascular tissue such as the bulbar conjunctiva or sublingual mucosa. In this manner, blood vessels can be directly observed using optical or Doppler techniques. Measurements such as cell movement, vessel morphometry, and vessel size are taken, and calculations made of microvascular blood flow and perfusion. Numerous groups have used such techniques to evaluate blood flow in various disease models in animals as well as in humans. A few have used the technique to evaluate blood flow in sickle cell patients, at baseline and in VOC, as well. Limited work has been done to evaluate changes in microvascular blood flow resulting from direct intervention, including 1 study in patients experiencing VOC who had improvement in microvascular blood flow resulting from treatment with an anti-adhesive agent (Poloxamer-188). Thus, the use of this non-invasive technique to document such responses to treatment in the context of SCD is promising.

### **1.4 Treatment of Vaso-Occlusive Crisis**

Nonpharmacologic management of pain includes cutaneous stimulation (transcutaneous electrical nerve stimulation), heat, cold, vibration, distraction, relaxation, massage, music, guided imagery, self-hypnosis, self-motivation, acupuncture, and biofeedback.

Pharmacologic management of pain includes the use of 3 major classes of compounds: non-opioids (nonsteroidal anti-inflammatory drugs [NSAIDs], topical agents, tramadol, and corticosteroids), opioids, and adjuvants

(antihistamines, antidepressants, benzodiazepines, and anticonvulsants). Adjuvant treatments for pain are typically used for chronic pain. NSAIDs are the first line of therapy for acute VOC pain, and are typically prescribed on an outpatient basis. Opioids in repeated and increasing doses are the first line of treatment for emergency department or inpatient care required for acute VOC. Common drugs include codeine (oral, for mild pain); or for moderate to severe pain, IV morphine, or morphine-equivalent opioids such as oxymorphone, levophanol, meperidine, fentanyl, and methadone. Opioid agonists may also be used in the management of sickle cell pain in adults. They decrease or modify the perception of pain at the level of the CNS.

Other supportive measures for VOC include hydration, transfusion, and treatment of any concurrent infections. No treatment is available to interfere with the sickling or vaso-occlusive process.

Current long-term medical management of SCD includes use of hydroxyurea, which is used to increase Hb F concentration and reduce the number of pain crises by preventing their development.

## **1.5 Nonclinical Information**

A summary of nonclinical studies is provided in the following sections. Additional information may be found in the Investigator's Brochure.

### **1.5.1 Pharmacology**

*In vitro* and *in vivo* pharmacodynamic studies demonstrate that GMI-1070 administration can inhibit selectin binding and biological activity as it relates to induction of selectin-mediated inflammation. *In vitro* studies have demonstrated that GMI-1070 blocked binding of all 3 selectins (E-, P-, and L-selectin), and inhibited the selectin-mediated leukocyte rolling and adhesion.

*In vivo* studies in a mouse model for SCD showed that treatment with 20 mg/kg of GMI-1070 increased blood flow, decreased adhesion of cells, and increased survival. In a delayed-type hypersensitivity model, treatment with GMI-1070 (10 and 20 mg/kg) inhibited T-cell migration to the site of inflammation. Administration of GMI-1070 (20 mg/kg IV) in the diabetic mouse model inhibited the inherent selectin-mediated increased rolling and adhesion of leukocytes. In an acute myocardial injury rate model, the infarct size is the result of a selectin-dependent inflammatory response. Administration of GMI-1070 (10 or 20 mg/kg IV) in this model resulted in a decrease in infarct size.

A CNS safety pharmacology study was conducted in CD-1 mice. No treatment-related effects were observed in the functional observational battery of tests when the mice were administered IV GMI-1070 (37.5, 150, or 300 mg/kg).

Results of 2 human ether-a-go-go-related gene assays with GMI-1070 (0.5, 1.0, 5.0, and 10.0 mg/mL for the first study; 0.5, 1.0, 3.0, 7.0, and 10.0 mg/mL for the second study) gave no evidence that GMI-1070 administration to humans would have any untoward effect on the cardiovascular system in regard to QT prolongation. These study results are consistent with the results of the 14-day repeat-dose toxicology study in cynomolgus monkeys noted below, in which IV administration of GMI-1070 (up to 75 mg/kg) had no apparent effect on QT intervals as determined by electrocardiogram (ECG).

### **1.5.2 Pharmacokinetics**

A single IV dose of GMI-1070 administered to mice (20 mg/kg), rats (20 mg/kg), and monkeys (150 mg/kg), showed rapid systemic exposure with a consistent time to maximum concentration ( $t_{\max}$ ) of 0.08 hours for all 3 species. Maximum concentration ( $C_{\max}$ ) was slightly lower in mice than rats (107.83 and 153.0  $\mu\text{g/mL}$ , respectively). The area under the curve ( $\text{AUC}_{(0-\infty)}$ ) was higher in rats (233.45 hours  $\mu\text{g/mL}$ ) than mice (107.12 hours  $\mu\text{g/mL}$ ), but the half-life ( $t_{1/2}$ ) was similar for mice, rats, and monkeys at 1.25 hours, 1.4 hours, and <3 hours, respectively.

### **1.5.3 Toxicology**

Acute (single dose) toxicity testing of GMI-1070 in mice (3, 10, 30, 100, or 300 mg/kg) and cynomolgus monkeys (18.75, 37.5, 75, and 150 mg/kg) showed no treatment-related effects. Therefore, no maximum tolerated dose was determined. Results of the 14-day repeat-dose IV toxicology study in mice indicated a no –observed –adverse effect level (NOAEL) of the highest dose tested, 150 mg/kg. The results of the 14-day repeat-dose IV toxicology study in cynomolgus monkeys showed a NOAEL of the highest dose tested, 75 mg/kg.

Results of the standard battery of genetic toxicology studies indicated that GMI-1070 is not mutagenic or genotoxic. In a local tolerance study of GMI-1070 in New Zealand White rabbits, GMI-1070 was administered by IV injection in the right marginal ear vein (300 mg/animal) and by perivascular injection adjacent to the left marginal ear vein (3 mg/kg). No evidence of treatment-related local injection site toxicity or irritation was observed.

## **1.6 Clinical Information**

A summary of clinical information is provided in the following sections. Additional information may be found in the Investigator's Brochure.

### **1.6.1 Safety**

Study GMI-1070-101 evaluated single doses of IV GMI-1070 at 2, 5, 10, 20, and 40 mg/kg. Study GMI-1070-102 evaluated multiple doses of 5, 10, and 20 mg/kg for 4 days, and a loading dose of 40 mg/kg followed by multiple doses of 20 mg/kg for 2 days. These studies were evaluated on a blinded basis in 72 healthy adult subjects (54 active, 18 placebo) as of 2 February 2009. GMI-1070 has demonstrated an excellent safety and tolerability profile after both single and multiple ascending doses as demonstrated by:

- No clinically significant ECG or physical exam findings
- All adverse events (AEs) were Grades 1 or 2
- No serious AEs (SAEs) occurred

Mild local irritation at the site of IV administration was observed to occur more frequently in higher dose groups with multiple doses. Two subjects in the high dose group of these Phase 1 studies have developed a rash. One subject is known to have received a dose of GMI-1070, 40 mg/kg. Assignment (to GMI-1070 or placebo) is still blinded for the second subject, but itching and spread of the rash required termination of dosing after 3 doses and treatment for itching. See Investigator's Brochure for details. None of these observations prevented dose escalation or progression to the next study.

It was therefore concluded by the investigator and the Medical Monitor that all doses observed in both studies demonstrated minimal safety concerns for continuing clinical trials at the tested dose levels, up to and including multiple doses of 20 mg/kg for 4 days and alternatively a loading dose of 40 mg/kg followed by 20 mg/kg for 2 days.

### **1.6.2 Pharmacokinetics**

In the single-dose study (GMI-1070-101), pharmacokinetics (PK) data showed detectable levels of drug, consistent PK parameters among subjects, and linear kinetics between groups. Plasma concentrations ( $C_{max}$ ) and  $AUC_{(0-t)}$  showed linear increases from the 2 mg/kg to the 40 mg/kg dose. Clearance (CL), renal clearance ( $CL_r$ ), apparent volume of distribution at the terminal phase ( $V_z$ ), and  $t_{1/2}$  did not change with dose. The mean value for  $CL_r$  ranged from 15.1 to 20.5 mL/minute, with an overall mean of 18.3 mL/min.  $CL_r$  was not dependent on plasma concentration. Over 90% of GMI-1070 was excreted in the urine.

In the multiple-dose study (GMI-1070-102), PK data are available for 3 dose levels: 5, 10, and 20 mg/kg. Key parameters on Days 1 and 5 for these groups ( $CL$ ,  $V_z$ , and  $t_{1/2}$ ) are consistent with those from the comparable dose level in Study GMI-1070-101.

Figure 2 below shows a semi-log graph of the single dose PK parameters from IV GMI-1070 at a range of doses from 2-40 mg/kg (GMI-1070-101 study).

[figure not shown]

Figure 2: IV GMI-1070 Pharmacokinetics with Single Dose in Volunteers: 2-40 mg/kg

## 2 STUDY OBJECTIVES AND PURPOSE

### 2.1 Rationale for this Study

GMI-1070 is a potent, rationally designed glycomimetic inhibitor of E-, P-, and L-selectins *in vitro*. GMI-1070 has been shown to inhibit inflammation in several animal models of disease, including the VOC of SCD. This investigational product is being developed for the treatment of VOC in SCD. In the present study, adult SCD patients who are not in VOC will be enrolled. In future clinical studies (not discussed here), IV GMI-1070 will be evaluated for safety and effect in sickle cell patients who are experiencing VOC.

Safety and PK data collected in the 2 prior studies of IV GMI-1070 in healthy volunteers have demonstrated an excellent safety profile and linear, predictable PK parameters at a range of doses for up to 4 days of treatment. The present

study seeks to build on this data by evaluating the safety, PK, and correlation with microvascular effect of 1 day of dosing with IV GMI-1070 in adult sickle cell patients who are at their stable medical baseline, not in VOC. The initial dose level being tested in this study is in the mid-range of those studied in the previous human studies, and subjects will receive 2 doses (1 day) of IV GMI-1070 as compared to 13 doses (4 days) in the previous multiple dose study. The starting dose level in this study, therefore, is substantially lower exposure to the study drug than in previous human studies. This data thus gives a solid platform to launch this current study as a reasonable first evaluation of IV GMI-1070 in sickle cell patients.

The rationale for the present study is to explore:

- Safety in the SCD population, and
- PK/pharmacodynamic relationships by correlation of blood levels of GMI-1070 with the effect on microvascular blood flow parameters in adults with SCD.

## **2.2 Study Objectives**

### **2.2.1 Primary**

- Evaluate the safety of multiple IV doses of GMI-1070 in adults with SCD.

### **2.2.2 Secondary**

- Evaluate the PK of multiple IV doses of GMI-1070 in adults with SCD.
- Evaluate the microvascular blood flow before and after treatment with IV GMI-1070 in adults with SCD.
- Evaluate biomarkers of adhesion, inflammation, and downstream selectin effect in the blood before and after treatment with IV GMI-1070 in adults with SCD.

## **3 STUDY DESIGN**

This will be an open-label, dose titration study of IV GMI-1070 in adults with stable SCD. Subjects will receive IV GMI-1070 at dose levels based on findings in earlier human studies. Study drug will be administered in the Clinical Research Center (CRC), day hospital, or equivalent clinical setting.

Titration for this study may be done either up or down and not necessarily in a step-wise fashion. At the beginning of the study, 4 subjects at each site will receive Dose Level A, which consists of a 20 mg/kg loading dose of IV GMI-1070 followed by a single 10 mg/kg dose of IV GMI-1070. Thus, subjects will

receive a total of 2 doses: 1 loading dose (20 mg/kg) in the morning at 0 hours, and 1 single dose (10 mg/kg) in the evening at  $10 \pm 1$  hours.

After these first 4 subjects at each site have been treated, safety, PK, and blood flow data from this first group will be reviewed by the investigator and the Medical Monitor. After this review, a site-specific decision will be made to do one of the following:

- Enroll 4 more subjects at this dose level (continue at Dose Level A); OR
- Enroll 4 subjects at the higher dose level (Dose Level B, 40 mg/kg loading dose followed by 20 mg/kg for 1 dose); OR
- Enroll 4 subjects at any of the 2 lower dose levels (Dose Level C, 10 mg/kg loading dose followed by 5 mg/kg for 1 dose; or Dose Level D, 5 mg/kg loading dose followed by 2.5 mg/kg for 1 dose).

Safety, PK, and blood flow data will be reviewed after completion of each group of 4 subjects at each site. At that time a decision will be made to do one of the following:

- Enroll 4 more subjects at the current dose level; OR
- Evaluate titration options and enroll 4 subjects at any other protocol-described dose level.

This process will continue until a total of 20 subjects have been treated with GMI-1070. Refer to Figure 3 in Section 3, Study Titration Flow, for a diagram of study drug dosing at each site.

Note: If enrollment at a site begins after other sites have enrolled in the study, the safety, PK, and blood flow information gained by early-enrolling site(s) may be used to modify dosing by later-enrolling site(s).

After Dose Level A has been administered to at least 4 subjects at one site, and this site's investigator and the Medical Monitor have determined it appropriate to proceed with another dose level as described above, a new site joining the study may proceed with either of the confirmed dose levels (Dose Level A, or the subsequent chosen dose level) if agreed by the new site's investigator and Medical Monitor.

Subjects will be evaluated in the clinic for up to 11 hours after administration of the first dose. Outpatient follow-up visits to the clinic will take place at  $24 \pm 3$  and  $48 \pm 12$  hours post first dose, and on Day  $7 \pm 2$  days. A telephone contact will be made at Day  $28 \pm 3$  days.

Plasma sampling for PK and IVM testing for microvascular blood flow will be performed at the following times:

- Predose (on the day of dosing), and
- $30 \pm 10$  minutes, and
- $2 \pm 0.25$ ,  $4 \pm 1$ ,  $8 \pm 2$ ,  $24 \pm 3$ , and  $48 \pm 12$  (PK only) hours after administration of the first dose of IV GMI-1070

Similarly, plasma sampling for research purposes (biomarkers for adhesion; plasma may be frozen for later research use related to this study) will be performed at the following times:

- Predose, and
- $4 \pm 1$ ,  $8 \pm 2$ ,  $24 \pm 3$ , and  $48 \pm 12$  hours after administration of the first dose of IV GMI-1070

[figure not shown]

**Figure 3: Study Titration Flow Chart**

## **4 SELECTION AND WITHDRAWAL OF SUBJECTS**

### **4.1 Number of Subjects**

The study plans to enroll 4 subjects at a time, up to a total of 20 subjects. An amendment will be considered to increase the total number of subjects if the data from the first 20 subjects support such an increase.

### **4.2 Inclusion Criteria**

To be eligible for inclusion, each subject must fulfill each of the following criteria at screening, and must continue to fulfill these criteria at baseline (if reassessed):

1. Age 18 to 50 years
2. Established diagnosis of SCD-SS or SCD-S $\beta^0$ -thal
3. Subject is at medical baseline, with no evidence of worsening of disease over the last 3 months (as determined by the investigator)
4. Expectation that the subject will be available and agree to return for follow-up visits for the full duration of the study
5. Ability to cooperate with IVM
6. Documented and observed written informed consent

### **4.3 Exclusion Criteria**

Subjects will be excluded from the study if any of the following criteria are met at screening or at baseline (if reassessed):

1. Weight of  $\geq 100$  kg at screening
2. Serum creatinine  $> 1.5$  mg/dL
3. Alanine transaminase (ALT/SGPT)  $> 2\times$  upper limit of normal (based on clinic lab normal range)
4. Hemoglobin  $\leq 6$  g/dL
5. VOC, defined as an episode requiring a visit to a medical facility resulting in medical treatment for pain, within the past 14 days
6. Recent (within the past 30 days) major surgery, hospitalization, documented bacterial infection requiring antibiotic treatment, or significant bleeding
7. Infection or inflammation at the site of probe placement as determined by investigator
8. Recent (within the past 90 days) cerebrovascular accident or seizure
9. Recent (within the past 60 days) transfusion of any type
10. Enrollment in a hypertransfusion program
11. Currently taking systemic steroids; use of inhaled steroids is acceptable. Use of hydroxyurea or NSAIDs is acceptable

12. Currently receiving, or has received within the previous 4 weeks, any other investigational agent
13. Pregnant or lactating female; or female of childbearing age unable or unwilling to comply with birth control or abstinence during the course of the study
14. Medical or psychiatric condition that, in the opinion of the investigator, may pose a risk to the subject for participation or interfere with the conduct or results of the study
15. Subjects with a history of alcohol or other substance abuse within the last year

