## STUDY SCHEDULE

Table 1: Schedule of Assessments

|                                             | Screening within 30 days | Pre-Dose Baseline | IV GMI-1070 Dosing |                                                  |          | Post Dosing    |                |                |                       |
|---------------------------------------------|--------------------------|-------------------|--------------------|--------------------------------------------------|----------|----------------|----------------|----------------|-----------------------|
|                                             |                          |                   | 0 hrs              | 30±10 min,
2±0.25 hrs,
4±1 hrs,
8±2 hrs | 10±1 hrs | 24±3 hrs       | 48±12 hrs      |                |                       |
| Visit                                       | Before Day 1             | Day 1             | Day 1              |                                                  |          | Day 2          | Day 3          | Day 7±2        | Day 28±3  |
| Informed consent                            | ✓                        |                   |                    |                                                  |          |                |                |                |                       |
| Inclusion/exclusion criteria                | ✓                        |                   |                    |                                                  |          |                |                |                |                       |
| Assignment to dose level                    |                          | ✓                 |                    |                                                  |          |                |                |                |                       |
| Demographics                                | ✓                        |                   |                    |                                                  |          |                |                |                |                       |
| Medical history                             | ✓                        | ✓                 |                    |                                                  |          |                |                |                |                       |

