## **5.2 Concomitant Medications**

All concomitant medications should be recorded at Screening, confirmed predose, and recorded again during the study visits. Subjects currently taking anti-inflammatory agents or steroids will be excluded from enrollment. The use of hydroxyurea and NSAIDs will be allowed.

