### **6.1.1 Screening Visit**

The Screening Visit should occur within 30 days prior to initiation of treatment. All prospective subjects will have the study explained in non-technical terms by a member of the research team or a member of the clinic staff. The nature of the drug substance to be evaluated will be explained together with potential hazards involving possible adverse reactions. Written informed consent will be obtained from each subject prior to dosing.

Subjects will have to meet all inclusion/exclusion criteria before being enrolled in the study (see Section 4).

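### Re-confirming eligibility on Day 1 is optional and unscheduled, although screening may precede dosing by 30 days and the VOC look-back is only 14 days

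*Protocol*

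**What the plan says.** Section 4.3 states: "Subjects will be excluded from the study if any of the following criteria are met at screening or at baseline (if reassessed". Section 4.2 treats the inclusion criteria alike: subjects "must continue to fulfill these criteria at baseline (if reassessed", and the synopsis repeats that proviso for inclusion.

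Section 6.1.1 sets the interval: "The Screening Visit should occur within 30 days prior to initiation of treatment". In Table 1 the row "Inclusion/exclusion criteria" is ticked at Screening and not at Pre-Dose Baseline.

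Several exclusions in Section 4.3 are look-backs. Item 5 concerns a VOC episode "resulting in medical treatment for pain, within the past 14 days". Item 6 reads "Recent (within the past 30 days) major surgery, hospitalization, documented bacterial infection requiring antibiotic treatment, or significant bleeding". Transfusion has a 60-day window and another investigational agent a 4-week window. Item 1 (weight) is pinned to screening by its own wording; the look-back items do not name the visit from which they count.

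On concomitant drugs, Section 5.2 states: "Subjects currently taking anti-inflammatory agents or steroids will be excluded from enrollment". Its next sentence permits hydroxyurea and NSAIDs. Section 4.3 item 11 excludes systemic steroids only and accepts inhaled steroids and NSAIDs.

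**The concern.** The trial is meant for adults with stable sickle cell disease who are not in VOC (Sections 2.1 and 3). The rule as worded lets a site treat the screening decision as final, and that decision may be older than the VOC window it enforces. Three sites could follow three practices and all comply.

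Stability at dosing matters because the study is open-label and unrandomised (Section 5.1.1), and the efficacy analysis models change from baseline (Section 9.2.3). Section 1.2 notes that soluble E-selectin and ICAM-1 are higher in acute VOC than at baseline. A subject settling after a recent crisis could therefore show a fall in biomarkers that has nothing to do with the drug. The dose review in Section 6.2.5 compares IVM before and after dosing in groups of four, so one such subject is a quarter of the evidence for the next dose. There is also a plain safety interest in knowing that subjects are stable on the day they are dosed.

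**Working it through.** The protocol gives no figure of its own for this risk and derives its 20 subjects from no formula, so there is nothing to reproduce. The check has three parts.

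**1. What a screening check covers.** If screening is g days before dosing and a criterion looks back W days, the part of the last W days before dosing that screening did not see is min(g, W). At the permitted maximum, g = 30:

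| Criterion (Section 4.3) | W (days) | Days before dosing not seen at screening |
|---|---|---|
| VOC | 14 | 14 of 14 |
| Other investigational agent | 28 | 28 of 28 |
| Surgery, hospitalisation, infection, bleeding | 30 | 30 of 30 |
| Transfusion | 60 | 30 of 60 |

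For VOC, any screening visit 14 or more days before dosing sees none of the relevant window. A check on Day -30 covers roughly Day -44 to Day -30.

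**2. What Day 1 adds.**
- Table 1 requires at Pre-Dose Baseline: medical history, targeted examination, vital signs, biochemistry and haematology, urinalysis, pregnancy test and concomitant medication.
- Section 5.2 has medications confirmed before dosing.
- Section 6.1.2.1 assigns eligible subjects to a dose level that day, but presupposes eligibility and schedules no decision on it.
- Section 6.1.1 requires all criteria to be met before enrolment, but does not tie enrolment to Day 1.
- Section 6.2.1.1 says what to do with a new clinically significant finding at the baseline examination: complete an adverse event form. It does not mention exclusion.
- Section 9.1 defines the Safety population by at least one dose and any follow-up, and the Efficacy population by at least one dose and one IVM measurement. Neither has an eligibility condition.

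The information is gathered, but the decision that should follow from it is not required.

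**3. How often an event could fall in the gap.** Section 1.2 says that over a year "about 60% of patients with SCD-SS will have at least 1 severe VOC". Assuming a constant hazard:
- λ = -ln(1 - 0.60) = 0.916 per year.
- Risk in d days: p = 1 - exp(-λd/365).
- d = 14: p = 1 - exp(-0.916 × 14/365) = 0.0345. Expected among 20: 20 × 0.0345 = 0.69. Chance of at least one in 20: 1 - (1 - 0.0345)^20 = 0.505; in a group of four, 0.131.
- d = 30: p = 0.0725. Expected among 20: 1.45.

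Varying the annual risk from 30% to 80%, an assumed range, gives p from 1.4% to 6.0% in 14 days and 0.27 to 1.20 expected among 20. Halving the hazard to allow for selection on stability, also an assumption, gives p = 1 - exp(-0.458 × 14/365) = 1.7%, or 0.35 expected among 20.

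**Steroids and anti-inflammatory drugs.** A subject on an inhaled steroid is eligible under Section 4.3 item 11 and excluded under Section 5.2 as worded. Within Section 5.2, anti-inflammatory agents are excluded in one sentence and NSAIDs allowed in the next.

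**The case against.** The strongest reply is that Day 1 would catch these events. The history and medication review are mandatory, and a recent crisis, infection or transfusion would normally come out in them. Once it has, that criterion has in effect been reassessed, and Section 4.3 then excludes the subject. The investigator must also sign a written authorisation before drug is provided (Section 5.1). Most of this stands. It means the gap in the wording will usually be closed in practice, though not that the protocol requires it to be closed.

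A reader might infer three stronger things that the documents do not support:
- That eligibility is settled at screening alone, so the plan admits a subject who had a VOC the day before dosing. The opening of Section 4.3 itself reaches baseline when criteria are reassessed. Such a subject would be dosed only if the Day 1 history missed the event or it was not acted on.
- That there is a 50% chance of dosing an unstable subject. That figure is the chance of at least one severe VOC in a 14-day gap among 20 subjects, with no allowance for detection on Day 1. No rate of missed detection can be had from the protocol.
- That Sections 5.2 and 4.3 conflict over NSAIDs. Both permit them. The NSAID inconsistency lies inside Section 5.2, and the conflict between the sections is over inhaled steroids.

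It is also fair to say that the bias is a possibility only. Section 1.2 gives no time course for biomarker recovery, and the protocol does not say how blood flow behaves after a crisis. The primary objective is safety.

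**Conclusion.** The point holds as a defect in a stated rule. Re-confirmation on Day 1 is optional under Sections 4.2 and 4.3 and absent from Table 1, over an interval that can exceed the VOC look-back. The data needed are already collected but not linked to a required decision, and any subject dosed despite an intervening event stays in the analysis populations.

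The gap events number about 0.7 among 20 for a 14-day interval. This rests on a constant hazard and on the 60% figure applying to these subjects. It is probably too high for patients selected for no worsening over 3 months. In the other direction, the 60% counts severe VOC only, while item 5 covers any facility visit with pain treatment, and infections, hospitalisations and transfusions come on top. The number of subjects dosed despite an event would be smaller and cannot be estimated from the document. No sample size, alpha or power figure is affected.

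The inhaled-steroid contradiction is a separate, definite conflict over who may enrol.

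**What to change.** - In Sections 4.2 and 4.3 and the synopsis, delete the reassessment proviso for the time-window, concomitant-drug and pregnancy criteria. The change need not extend to the laboratory criteria; the protocol does not say whether Day 1 results are available before the first infusion.
- Tick the eligibility row in the Pre-Dose Baseline column of Table 1, and say in Section 6.1.2.1 that assignment to a dose level follows that confirmation.
- State that the look-back windows also apply as of the first dose.
- Reconcile Section 5.2 with Section 4.3 item 11 on steroids, and the two sentences of Section 5.2 on anti-inflammatory agents and NSAIDs.

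The cost is protocol wording and one tick. No new procedure is needed, since the history, medication review and pregnancy test are already done at that visit. The downside is that an occasional subject is deferred or rescreened.
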